## Methods

### Study design

This is a randomized, multicenter, double-blinded, placebo-controlled trial involving 498 women diagnosed with vHSIL and scheduled for receiving treatment. Eligible participants will include women with histologically diagnosed vHSIL, both primary lesions and those with recurrence. Treatment follows current guidelines. Participants will be randomized to either receive adjuvant HPV vaccination or a placebo during treatment initiation, approximately two and six months into treatment (three dose regimen). All participants will undergo a two-year clinical follow-up as part of the trial. Throughout the study, participants will complete questionnaires, with Dutch participants optionally undergoing blood sampling to assess immune response three times. Participants may opt in to the blood sampling procedure, which is not obligatory for trial participation. Follow-up assessments adhere to current guidelines, and patients will receive standard treatment per the latest vHSIL guidelines. Long-term follow-up will examine vaccine efficacy after 5 and 10 years, along with the occurrence of vulvar malignancies (Figure 1 in Appendix).

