### Materials and equipment

The adjuvant HPV vaccine to be administered is the nonavalent HPV vaccine, which is globally approved and utilized in national immunization programs for children. The nonavalent HPV vaccination is an adjuvant non-infectious recombinant 9-valent vaccine. It is prepared from the highly purified virus-like particles (VLPs) of the major capsid L1 protein from the same four HPV types (6, 11, 16, 18) in the qHPV vaccine Gardasil or Silgard and five additional HPV types (31, 33, 45, 52, 58). It uses the same amorphous aluminum hydroxyphosphate sulfate adjuvant as the qHPV vaccine. The VLPs cannot infect cells, reproduce, or cause disease. The efficacy of L1 VLP vaccines is thought to be mediated by the development of a humoral immune response.

The placebo consists of physiological saline (NaCl) with no active ingredients. Preparation and labeling of the investigational medicinal products will be done according to the relevant GMP guidelines. The labels will be in Dutch for the Dutch centers (according to the CCMO rules) and will be translated into the language of each participating country. Distribution will be organized by the Erasmus MC Pharmacy.

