### Randomization, stratification, blinding and treatment allocation

Randomization will be performed through the secure web-based interface Castor EDC (Castor Electronic Data Capture available at: https://castoredc.com). Patients will be randomly assigned to either adjuvant HPV vaccination or placebo in a 1:1 ratio. Randomization will be stratified by country of inclusion, treatment group (surgery, laser vaporization, and topical imiquimod), and the first episode of vHSIL versus recurrence. The study team, the local investigator, and the patient are blinded for treatment allocation of the study medication. The allocated medication in the Netherlands will be prepared by the pharmacy at the Erasmus MC and administered to the patient by a designated study team member from Erasmus MC. Study medication will be masked for the administrator of the vaccination and the patient.

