### Data analysis

The primary outcome will assess the relative risk of vHSIL recurrence within 24 months, analyzing the efficacy of adjuvant nonavalent HPV vaccination using logistic regression methods adjusted for country of inclusion, treatment types, and primary versus recurrence vHSIL. A 95% confidence interval will be estimated for the odds ratio, with significance determined by a likelihood ratio test. *P*-values below 0.05 will be considered statistically significant.

Analysis of secondary endpoint(s) Secondary objectives 1, 2, 4, 9, and 10 will be analyzed similarly to the primary endpoint, using logistic regression methods adjusted for the stratification variables: country of inclusion, treatment types, and primary versus recurrence vHSIL. 95% Confidence intervals will be estimated for the odds ratios and significance will be determined using likelihood ratio tests. *P*-values below 0.05 will be considered statistically significant.

Secondary objectives where the effectiveness of vaccination is compared between different patient groups (secondary objectives 3 and 5) will be analyzed using logistic regression methods adjusted for stratification variables. 95% Confidence intervals will be estimated for the odds ratio, and significance will be determined using a likelihood ratio test. *P*-values below 0.05 will be considered statistically significant.

Secondary objective 6 will be analyzed using a linear regression model to determine the difference in log-transformed antibody levels at baseline and after placebo or vaccination and adjusted for stratification variables. The impact of change in antibody levels on the primary endpoint will be analyzed using a logistic regression model adjusted for stratification variables. 95% Confidence interval will be estimated for the coefficients, and significance will be determined using a likelihood ratio test. *P*-values below 0.05 will be considered statistically significant.

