Secondary objective 8: Quality of Life will be measured at several time points. They will be assessed with a Euroqol 5D-5L questionnaire. Sexual health will be evaluated using FSFI. The impact of vaccination on these measures over time will be analyzed using linear mixed-effect models, with vaccination status and stratification variables as fixed effects and random intercepts as random effects. Additional random effects will be selected based on likelihood ratio tests. A 95% Confidence interval will be estimated for the coefficients, and significance will be determined using a likelihood ratio test. *P*-values below 0.05 will be considered statistically significant.

Secondary objective 7: Cost-effectiveness will be assessed by calculating the incremental cost-effectiveness ratio (ICER), which is defined as the difference in costs divided by the average change in the effectiveness of the vaccine versus placebo following vHSIL treatment. A Budget impact analysis (BIA) will be performed, in accordance with the principles for good practice for BIA, to address the financial stream of consequences to assess the affordability of offering the vaccine following vHSIL treatment.

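### The antibody–recurrence model has no arm term and no stated restriction to vaccinated women, so if the vaccine works it will tend to credit antibody rise with the effect of randomisation

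*Protocol article*

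**What the plan says.** The Data analysis section describes two analyses under secondary objective 6. The first is a linear model for the "difference in log-transformed antibody levels at baseline and after placebo or vaccination". The second links antibodies to the clinical outcome: "The impact of change in antibody levels on the primary endpoint will be analyzed using a logistic regression model adjusted for stratification variables". Confidence intervals, a likelihood ratio test and a 0.05 threshold are attached, and the analysis is not labelled exploratory.

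The same section spells out the covariates when it describes other secondary objectives: "adjusted for the stratification variables: country of inclusion, treatment types, and primary versus recurrence vHSIL". The randomisation section lists the same three factors: "Randomization will be stratified by country of inclusion, treatment group (surgery, laser vaporization, and topical imiquimod), and the first episode of vHSIL versus recurrence". Arm is in neither list.

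Two further facts matter. Under Materials and equipment, "The placebo consists of physiological saline (NaCl) with no active ingredients". Under Study design, antibodies are measured in a subset, "with Dutch participants optionally undergoing blood sampling to assess immune response three times"; the size of that subset is not stated.

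**The concern.** In the primary model arm can go unlisted among the covariates because arm is the exposure. In the antibody–recurrence model the exposure is antibody change, so an unlisted arm is, on the face of the text, absent.

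A vaccine given to one arm and saline to the other makes antibody change a proxy for allocation. Pooling the arms without an arm term then mixes two questions: whether vaccination lowers recurrence, and whether women with a larger antibody rise recur less. The first is already answered by the randomised comparison. The second is what a model of the impact of antibody change is meant to address, and the pooled slope cannot separate it from the first. The coefficient would be negative whether antibodies carry the protection or have nothing to do with it.

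At stake is the interpretation of one secondary analysis. A positive trial could report antibody rise as related to protection on evidence that shows only that the vaccine worked.

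**Working it through.** The plan gives no figure for this model, so there is none to reproduce. The check asks how the stated model behaves when titre has no relation to recurrence within either arm.

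**Inputs from the protocol article.** Recurrence 19% versus 32% (Sample size calculations); 1:1 allocation; likelihood ratio test at 0.05; 249 per arm in the whole trial, which is the ceiling for the subset.

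**Assumed inputs.** Number of women sampled; antibody change on the log10 scale, with mean shift Δ in the vaccine arm, zero in the placebo arm, and standard deviations s_v and s_p.

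**Step 1, size of the arm effect.** Odds are 0.19/0.81 = 0.2346 and 0.32/0.68 = 0.4706. The odds ratio is 0.2346/0.4706 = 0.498 and its logarithm is −0.696.

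**Step 2, what the pooled slope estimates.** With 1:1 arms, the share of the variance of antibody change that lies between arms is λ = (Δ²/4) / (Δ²/4 + (s_v² + s_p²)/2). The correlation of antibody change with arm is √λ. If recurrence depends on arm only, the pooled slope per log10 is approximately (−0.696/Δ) × λ.

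- Δ = 2, SDs 0.5 and 0.2: λ = 1/(1 + 0.145) = 0.873, correlation 0.93. Slope = −0.348 × 0.873 = −0.304, odds ratio 0.74.
- Δ = 1, SDs 1.0 and 0.5: λ = 0.25/(0.25 + 0.625) = 0.286, correlation 0.53. Slope = −0.696 × 0.286 = −0.199, odds ratio 0.82.

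The true within-arm odds ratio is 1 in both cases.

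**Step 3, how often the test rejects.** Simulated trials, recurrence depending on arm only, arm not in the model:

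| Women sampled per arm | Δ = 2, SDs 0.6/0.2 | Δ = 2, SDs 0.5/0.2, adjusted for treatment type and episode |
|---|---|---|
| 25 | 18% | – |
| 40 | 24% | – |
| 50 | 29% | 33% |
| 100 | about 50% | 52% |
| 150 | 67–69% | 68% |
| 199 | – | 80% |
| 212 | 82–83% | – |
| 249 | – | 88% |

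In the right-hand column the median odds ratio per log10 is 0.71–0.73, in line with step 2.

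**Step 4, sensitivity.** With Δ = 1 and SDs 1.0/0.5 the rejection rate is 22% at 100 per arm and 38% at 212. With Δ = 3 and SDs 0.5/0.2 it is 84% at 199 per arm. With a weaker vaccine effect, 25% versus 32%, it is 17% at 100 per arm and 30% at 212. The median odds ratio stayed below 1 in every titre scenario tried at 199 per arm (0.63–0.81).

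**Step 5, with arm included.** On the same simulated data as the right-hand column, adding arm gives rejection in 4.5–6.5% of trials and a median odds ratio of 0.97–1.01.

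**Step 6, inert vaccine.** With equal recurrence in both arms, the model without arm rejects in 4.6–5.6% of trials. No artefact arises.

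**The case against.** The strongest reply is that the wording is terse and arm may be meant. The linear antibody model also lists only stratification variables, yet it evidently compares arms. The quality-of-life model, which does name the arm ("with vaccination status and stratification variables as fixed effects and random intercepts as random effects"), is the exception and not the rule. That contrast is therefore weak evidence by itself. What remains is that, in the sentence at issue, antibody change occupies the place of the exposure. Nothing in it supplies arm as a second term.

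A second reply is that the model may be intended for vaccinated women only. The matching secondary endpoint speaks of antibody change after vaccination and then asks about a correlation with recurrence, which is compatible with that reading. It is possible but not stated, and the sentence just before the logistic model covers both arms: "to determine the difference in log-transformed antibody levels at baseline and after placebo or vaccination". A full analysis plan could settle the matter. The article nevertheless fixes an adjustment set, and an analyst who followed it literally would pool the arms without an arm term.

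Third, the size depends on unknowns. This stands: sampling is optional and Dutch only, so the subset may be small, and the titre distributions are assumed. The direction of the bias does not depend on them, provided the vaccine raises titre and lowers recurrence.

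Fourth, the protocol uses antibodies as a surrogate for immune response and does not claim that they mark protection against recurrence. This also stands. The risk lies in how a significant coefficient would be read.

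**Conclusion.** The point holds conditionally. As written, the model cannot separate a titre–recurrence relation from the effect of vaccination. If the vaccine reduces recurrence, which is the trial's own hypothesis, the pooled coefficient is biased toward apparent protection. At 32% versus 19%, and with no within-arm relation, the false-positive rate is roughly 18–30% at 25–50 women per arm, about 50% at 100 and about 80% at 200, or about 22–38% at 100–212 with a smaller, noisier titre shift. With arm included it is about 5%. Subset size and titre distributions are assumptions.

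A reader might infer more than this, and the documents do not support it:

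- That antibody change will appear protective whatever the vaccine does. With an inert vaccine the test keeps its nominal level.
- That comparing arms on change from baseline is an error. That comparison is unbiased under randomisation, adjustment for baseline is a matter of precision, and the wording does not clearly fix a change score.
- That listing country in a Dutch-only subset is harmful. A constant covariate drops out and alters no estimate.
- That the primary result is affected. It is not.

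This is a correction worth making to one secondary analysis in an optional subset.

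**What to change.** State in the plan that the antibody–recurrence model either includes randomised arm as a covariate or is fitted in vaccinated women only. Report the resulting within-arm association as exploratory, because antibody rise within an arm is not randomised.

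This changes wording only and needs no new data. The cost is a wider confidence interval for the antibody association, since the between-arm difference no longer contributes to it and the placebo arm adds little variation in titre.

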### Study objectives and endpoints

The primary objective is to evaluate the efficacy of adjuvant nonavalent HPV vaccination in women who will undergo treatment for (histologically proven) vHSIL in preventing clinical recurrence of vHSIL up to 24 months.

The second objectives are:The effectiveness (complete remission) after treatment in patients receiving vaccination versus placebo at 6 and 12 months.Complete remission after treatment in patients receiving vaccination versus placebo at 6 and 12 months in primary episode (newly diagnosed) vHSIL versus recurrence.The effectiveness of adjuvant vaccination in different treatments of vHSIL (laser, imiquimod, excision) after 24 months.Additional treatment for vHSIL needed in the study period, and differences between the study groups.The effect of vaccination versus placebo on different hrHPV types (HPV type of primary and recurrence).The difference in immune response to HPV vaccination versus placebo vaccination. (We use HPV antibodies as a surrogate marker for immune response. Peripheral blood mononuclear cells (PBMCs) are bio banked for the possibility to measure in-depth cellular immune response at the molecular level at the end of the trial).Cost-effectiveness (IMTA Medical Consumption Questionnaire (iMCQ) and IMTA Productivity Cost Questionnaire (iPCQ) will be used).Quality of life (measured by Euroqol 5D-5L questionnaire) and sexual health (measured by Female Sexual Function Index, FSFI questionnaire) improved after vaccination compared to placebo.The effect of vaccination versus placebo on CIN/cervical cytology of the uterine Cervix.Long-term follow-up: The difference between HPV vaccination and placebo group in number of recurrences of vHSIL (5 and 10 years) and vulvar malignancies (2,5 and 10 years).

The primary endpoint is a difference in the number and percentage of patients with a clinical recurrence rate of vHSIL between HPV vaccination and placebo up to 24 months post-treatment.

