The secondary endpoints are:Difference in the number and percentage of patients with a clinical recurrence rate of vHSIL between HPV vaccination and placebo at 6 and 12 months.Difference in the number and percentage of patients with a clinical recurrence rate of vHSIL between HPV vaccination and placebo at 6 and 12 months for primary vHSIL versus recurrent vHSIL.Difference in the number and percentage of patients with a clinical recurrence rate of vHSIL between the different treatment modalities.Difference in number and percentage for additional treatment necessary after primary treatment.Description and percentage of different hrHPV types. Percentage clearance of primary HPV type for vaccination versus placebo.Concentration of HPV antibodies and percentage of increase or decrease after vaccination.Is there a correlation between the number or percentage of recurrence? Is that different in primary versus recurrence episodes of vHSIL.Incremental cost-effectiveness ratio (ICER) describes the difference in costs and budget impact analysis.Description and change in numeric value and percentage in different score forms questionnaires. Percentage increase of decreased quality of life, sexual impact, and productivity impact.Difference in number and percentage of HPV types in cervical cytology and vHSIL before and after vaccination.Difference in number and percentage in the recurrence rate of vHSIL and vulvar cancer between HPV vaccination and placebo. Other HPV-related diseases known?

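### As written, the antibody–recurrence model has no randomised-arm term and no restriction to vaccinated women, so a significant coefficient could reflect the vaccine effect alone

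*Protocol article*

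**What the plan says.** Under Data analysis, the article gives two models for secondary objective 6. The first is a linear regression for the "difference in log-transformed antibody levels at baseline and after placebo or vaccination and adjusted for stratification variables". The second is the one at issue: "The impact of change in antibody levels on the primary endpoint will be analyzed using a logistic regression model adjusted for stratification variables". Significance is by likelihood ratio test at P < 0.05.

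The same section spells out what the adjustment set contains: "adjusted for the stratification variables: country of inclusion, treatment types, and primary versus recurrence vHSIL". This matches the randomisation section: "Randomization will be stratified by country of inclusion, treatment group (surgery, laser vaporization, and topical imiquimod), and the first episode of vHSIL versus recurrence".

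Blood is not taken from everyone. The Study design section has "Dutch participants optionally undergoing blood sampling to assess immune response three times", and gives neither the number expected nor the sampling dates. The Materials and equipment section describes the placebo as saline without active ingredient.

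The list of secondary endpoints appears to state the purpose of the second model, in a sentence that is incomplete: "Is there a correlation between the number or percentage of recurrence".

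**The concern.** The second model puts antibody change where treatment normally stands, and adjusts only for the strata. If women from both arms enter it, the exposure has two sources of variation. One is the gap between vaccinated and saline-injected women, and the other is the spread among women within an arm. Only the second says whether women with a stronger response recur less often. With an inert comparator the first source dominates, so the coefficient mostly repeats the vaccine-versus-placebo comparison in a small opt-in subset.

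What is at stake is interpretation. If the vaccine lowers recurrence by any route, the plan can return a significant impact of antibody change on recurrence even when antibody level is irrelevant among vaccinated women. A reader could take that as evidence that the antibody response matters for recurrence.

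**Working it through.** **What the text fixes.** The outcome is the primary endpoint, the exposure is change in antibody levels, the covariates are the strata, and the test is a likelihood ratio test at 0.05. The article gives no sample size or power for this model, so there is no figure of its own to reproduce.

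**Is arm implied?** The article's other logistic models also mention only adjustment for strata, but there vaccination is itself the exposure. Here the named exposure is antibody change, so reading the sentence the same way leaves arm out. The quality-of-life model does list arm separately from the strata: "with vaccination status and stratification variables as fixed effects and random intercepts as random effects". That comparison is only suggestive, because arm is the exposure there. The adjustment set also looks carried over from the main models: if only Dutch participants are sampled, country of inclusion is presumably constant and adjusts for nothing.

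**Inputs for the illustration.**
- From the article (Sample size calculations): recurrence 32% without and 19% with vaccination.
- Assumed: log10 antibody rise with mean D = 1.0 to 2.0 and SD 0.5 in the vaccine arm; mean 0 and SD 0.2 in the placebo arm; equal numbers per arm; 50 or 100 sampled women per arm.
- Imposed: no relation between antibody change and recurrence within either arm.
- Strata are left out for simplicity.

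**Step 1: how far antibody change encodes arm.** With equal arms the between-arm variance is D²/4 and the mean within-arm variance is (0.5² + 0.2²)/2 = 0.145. The share explained by arm is R² = (D²/4) / (D²/4 + 0.145).
- D = 1: 0.25 / 0.395 = 0.63
- D = 2: 1 / 1.145 = 0.87

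**Step 2: how often the pooled model is significant.** Simulation with 2,000 trials per setting, logistic regression and likelihood ratio tests:

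| Sampled women per arm | Antibody change, no arm term | With arm term, or vaccine arm only |
|---|---|---|
| 50 | 23–29% | about 5% |
| 100 | 42–50% | about 5% |

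**Step 3: check by hand.** The arm difference has z = 0.13 / √[(0.32×0.68 + 0.19×0.81)/n].
- n = 50: 0.13 / 0.0862 = 1.51
- n = 100: 0.13 / 0.0610 = 2.13

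A proxy with correlation √R² to arm keeps about z√R², and the chance of significance is about Φ(z√R² − 1.96).
- n = 50: √0.63 gives z = 1.20 and Φ(−0.76) = 22%; √0.87 gives z = 1.41 and Φ(−0.55) = 29%.
- n = 100: z = 1.70 gives Φ(−0.26) = 40%; z = 1.99 gives Φ(0.03) = 51%.

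These agree with the simulation to within about two percentage points. They also show the mechanism: the pooled test is a diluted version of the arm comparison.

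**Step 4: sensitivity.** With other assumed distributions (vaccine-arm rise 2 to 6 log units, SD 1; placebo SD 0.3) and 150 women in total, 33–46% of trials were significant without an arm term and 5–6% with one. The size moves with the assumptions; the direction does not.

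**The case against.** The strongest reply is that the article does not say the arms are pooled. The phrase naming both placebo and vaccination belongs to the sentence on the linear model, and the antibody–recurrence sentence gives no analysis set. A condensed article often names only adjustment covariates, and an unseen analysis plan may restrict this model or add arm. This stands to the extent that pooling is an inference. It does not remove the point: the article names the exposure, covariates and test, so this is a specified model, and followed as written it contains neither arm nor a restriction.

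A second reply is that the percentages are not false-positive rates in the strict sense. The marginal association between antibody change and recurrence really is non-null when the vaccine works, and a pooled model does estimate a correlation. That is correct. The percentages show how often a vaccine effect alone would surface as an antibody effect. What the pooled model cannot isolate is the relation within an arm.

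Third, the size rests on assumed antibody distributions and an unknown subset. That also stands. One can obtain much higher percentages by giving all or most of the 498 women an antibody result, but the article does not support this, because sampling is voluntary and confined to one country's participants.

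Finally, a reader might infer that the article claims antibodies as a correlate of protection. It does not. It says "We use HPV antibodies as a surrogate marker for immune response", which concerns immune response and not recurrence.

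**Conclusion.** The point holds in a limited form. Read as written, the model lets antibody change stand in largely for allocation, so a significant coefficient could reflect the vaccine effect and nothing more. Under the stated assumptions this happens in roughly a quarter of trials with 50 sampled women per arm and in just under half with 100, against about 5% once arm is handled. The conclusion rests on the inference that the arms are pooled, on little antibody rise after saline, and on a vaccine effect near the planned one.

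It would be too strong to say that the trial's main result is compromised: the primary comparison is by randomised arm and is untouched. It would also be too strong to prescribe which blood sample to use, or to count only recurrences after it, since the article gives no sampling dates on which to base such a rule. This is a low-to-moderate priority change to one secondary analysis.

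**What to change.** State the analysis set and the arm handling for this model. Suggested wording: *The association between change in antibody levels and recurrence is estimated among women allocated to vaccine (or in both arms with randomised arm included as a covariate), adjusted for the stratification variables, and is reported as an exploratory, non-randomised association.* Do not fit antibody change across both arms without arm.

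The change is to wording only and needs no new data or visits. Its statistical cost is precision. The vaccine-arm analysis uses about half of the sampled women. The two-arm version suffers from collinearity: the variance inflation factor 1/(1 − R²) is 1/0.367 = 2.7 at D = 1 and 1/0.127 = 7.9 at D = 2. Either way the interval will be wide, and the estimate will still not show that the antibody response causes any protection.

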### Data collection

All data will be collected using an electronic Case Report Form (eCRF) and electronic questionnaires. Data from the eCRF and questionnaires will be collected and stored using Castor EDC. Sequential subject numbers will be assigned to enrolled participants in the study. Access to stored data will be restricted solely to the principal and coordinating investigators of each participating center.

Demographic and baseline disease characteristic data will be summarized for each treatment group and consist of age, parity, cervical cytology and HPV status, prior treatment for vHSIL, prior treatment for cervical HSIL, smoking, and co-morbidities in which we focus on auto-immune diseases and history of cancer.

At each follow-up visit, the following data will be collected: visual/physical examination and preferably photo documentation of the vulva. If there is any suspicion of recurrence of vHSIL, a biopsy will be taken for histology and HPV typing endpoint, cervical cytology, and if additional treatment will be started.

At the start of the study, after 6, 24, and 60 months, patients will be asked to fill out questionnaires.

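### The quality-of-life and sexual-function model is meant to show the effect of vaccination over time, but lists no visit, vaccination-by-visit or baseline-score term

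*Protocol article*

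**What the plan says.** All references are to the Methods of the protocol article.

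- **Objective** (Study objectives and endpoints, secondary objective 8): quality of life and sexual health "improved after vaccination compared to placebo".
- **Endpoint** (same section, secondary endpoints): "Description and change in numeric value and percentage in different score forms questionnaires".
- **Timing** (Data collection): "At the start of the study, after 6, 24, and 60 months, patients will be asked to fill out questionnaires". One of the four questionnaires is therefore a baseline measurement.
- **Aim of the analysis** (Data analysis, secondary objective 8): "The impact of vaccination on these measures over time will be analyzed using linear mixed-effect models".
- **Model** (same paragraph): "with vaccination status and stratification variables as fixed effects and random intercepts as random effects".
- **Permitted extension** (same paragraph): "Additional random effects will be selected based on likelihood ratio tests". No step for adding fixed effects is given.
- **Stratification variables** (Randomization, stratification, blinding and treatment allocation): "Randomization will be stratified by country of inclusion, treatment group (surgery, laser vaporization, and topical imiquimod), and the first episode of vHSIL versus recurrence". Time is not among them.

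**The concern.** The stated model does not match its stated aim. With arm as the only vaccination term, the model yields one number per questionnaire: the arm difference averaged over whatever visits are in the data. That number is neither a change from baseline nor a difference at any named visit.

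What it means also depends on how the baseline questionnaire is used, which the article does not say. If baseline is one of the outcome rows, the average includes a visit at which randomisation makes the expected difference zero, and a real effect is understated. The one permitted extension does not help: a random slope for time added without a fixed time effect would force the mean slope to zero.

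At stake is a real benefit in EQ-5D-5L or FSFI being reported as smaller than it is, or missed, although the data needed to avoid this are already being collected.

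**Working it through.** The article gives no effect size, power or precision for these questionnaires, so there is no figure of its own to reproduce. The 498 was set for the recurrence endpoint and plays no part here beyond supplying the number per arm.

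**Inputs from the article:** 249 per arm, two-sided alpha 0.05, questionnaires at 0, 6, 24 and 60 months.

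**Assumptions:** total SD 1; equal correlation rho between any two visits (a random intercept implies this); no true arm difference at baseline; a constant effect d = 0.25 SD at every later visit; complete data. The 249 already includes an allowance for loss to follow-up, so complete data at 249 is generous to every option below.

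**1. Size of the coefficient if baseline is an outcome row.** With T visits the coefficient estimates [0 + (T − 1)d]/T = d(T − 1)/T, whatever rho is.
- Four visits: 0.75 × 0.25 = 0.1875.
- Three visits (0, 6, 24 months): 0.667 × 0.25 = 0.167.

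An exact generalised least squares calculation gives the same values. Adding a time main effect alone leaves both unchanged; the dilution goes only when the vaccination effect is confined to post-baseline visits or baseline becomes a covariate. A small simulation (40 runs, four visits) gave a ratio of 0.78 with complete data, consistent with 0.75 within simulation error, and 0.70 when response fell to 90%, 80% and 60% at the later visits.

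**2. Power with four visits, rho = 0.5.** Standard error = √(2 × per-arm variance/249); power = Φ(effect/SE − 1.96).

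| Analysis | Effect | Per-arm variance | SE | Power |
|---|---|---|---|---|
| As listed, baseline as an outcome row | 0.1875 | (1 + 3 × 0.5)/4 = 0.625 | 0.0709 | 75% |
| As listed, baseline left out | 0.25 | (1 + 2 × 0.5)/3 = 0.667 | 0.0732 | 93% |
| Follow-up mean adjusted for baseline | 0.25 | 0.667 − 0.5² = 0.417 | 0.0579 | 99% |
| One follow-up visit adjusted for baseline | 0.25 | 1 − 0.5² = 0.75 | 0.0776 | 90% |

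Change scores averaged over follow-up have variance 0.667 + 1 − 2 × 0.5 = 0.667, so at this correlation they match the second row.

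**3. Sensitivity to the assumed correlation** (rho from 0.3 to 0.7, same d and n):
- Four visits: 86% down to 66% as listed with baseline as an outcome row, against about 99% or more for the baseline-adjusted follow-up mean.
- Three visits: 72% down to 55%, against 96% to more than 99%.

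**The case against.** **The article is condensed and does not call its list of terms complete.** Coding of visits and handling of baseline are often left to the analysis plan, which may exist and is not shown. A further random effect would most naturally be a slope for time, which hints that time is in the model. This has some force, and the full plan may already resolve the point. But the article does not defer the model: it names the fixed effects, the random effects, the selection rule and the test. What it names cannot deliver the effect over time that the same paragraph announces.

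**The dilution rests on something the article does not say.** This stands. A reader might infer that the plan certainly shrinks the effect. It does so only if baseline is an outcome row. That is the natural reading, since no baseline covariate is listed, but if change scores are the outcome or baseline is dropped there is no dilution.

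**Vaccination status might mean doses received, or a variable coded 0 at baseline and 1 afterwards in the vaccine arm.** Neither is well supported: the Abstract states intention-to-treat principles, which points to the randomised arm. The time-varying coding would produce a different bias, because without a time term, change common to both arms loads onto vaccination. An assumed common shift of 0.5 SD would turn a true 0.25 SD into 0.57 to 0.69. This is a reason to tidy the wording, not a separate fault.

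**The power contrast is illustrative.** This also stands. A bleaker contrast can be had by using three visits and fewer women, but the article gives four questionnaire times and 249 per arm. Under the main reading the coefficient is still centred on zero when there is no effect, so the problem is understatement and not false positives.

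**Conclusion.** The point holds as a mismatch between model and aim for one secondary objective. On every plausible reading the listed model gives no effect by visit and makes no use of the baseline score as a covariate.

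The consequence depends on the handling of baseline. As an outcome row, it reduces the coefficient to 3/4 of a constant post-baseline effect with four visits, or 2/3 with three; this factor needs balanced, complete data and a constant effect, but no value for the correlation. If baseline is left out, the loss is one of precision and of information by visit: about 93% power against 99% in the illustration. The power figures rest on the assumed 0.25 SD and correlation, and should be read as showing direction and rough size.

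The primary analysis and the 498 are not touched.

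**What to change.** State the model for secondary objective 8 as follows: outcome, the post-baseline scores; fixed effects, randomised arm, categorical visit, arm-by-visit, baseline score and the stratification factors; random effect, an intercept per woman. A constrained-baseline longitudinal model, with baseline kept as an outcome and no arm difference allowed there, is an equivalent choice. A visit main effect alone would not be enough.

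Report the arm difference with its 95% confidence interval at each follow-up visit. The sponsor should choose the time point of main interest, or the average over follow-up, in advance; the article fixes none for this objective, and a single-visit contrast has less power than the average (about 90% against 99% in the illustration). Write randomised arm in place of vaccination status.

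The cost is a sentence or two of analysis wording and a few extra model terms, with no new data.
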